**Inclusion criteria**
Aged above 19 and under 80 Diagnosed of first-onset subcortical or brainstem ischemic stroke with imaging within 90 days Upper Extremity FMA score exceeds 15 points K-MMSE score of 15 or higher
**Exclusion criteria**
Among Upper Extremity FMA scores, those with a wrist score of less than 1 and a hand score of less than 1 Diagnosed with a cerebellar stroke With a history of cerebrovascular surgery With a history of psychiatric or neurological diseases before the onset of stroke Unable to undergo rehabilitation treatment due to other reasons, such as medical problems With a history of epilepsy or seizure disorder

FMA, Fugl-Meyer Assessment; K-MMSE; K-Mini Mental Status Exam.

All participants received detailed information about the trial and written informed consent was obtained. The research protocol has been approved by the institutional review boards of Seoul National University Bundang Hospital (IRB no: E-2010-642-001) and Chungnam National University Hospital (IRB no:2022-04-014). This study will be conducted in accordance with the Good Clinical Practice regulatory standards and the Declaration of Helsinki. The study protocol has been registered on the ClinicalTrials.gov, on September 10, 2022 (Identifier: NCT05535504).

### Randomization and blinding

2.3.

A list of random assignments will be prepared by a statistician who is independent of the research team. Within each institution, the participants will be stratified into two subgroups based on a baseline UE-FMA score of 28 using a stratified block randomization method with blocks of size 2 within each stratum, and the assignment ratio of the intervention and control groups will be maintained at 1:1. A random assignment list will be generated using SPSS version 23.0(IBM Corp., Armonk, NY, United States). The block size and seed number used will be randomly selected by a statistician responsible for the random assignment. Random assignments will be stored in opaque envelopes for each participant and delivered to the coordinator at the start of the intervention.

This clinical trial will be performed in a double (participant and evaluator) blind-fold manner, and the therapists who perform the treatment will also be blinded throughout the study. Owing to the nature of this clinical trial, the investigator who will perform rTMS will not be blinded to the assigned group.

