### Study design

2.1.

In this prospective, multi-center, double-blind, randomized sham-controlled, superiority trial, the effectiveness of low-frequency rTMS over the contralesional M1 will be compared to that of sham rTMS in patients who require upper limb rehabilitation due to subcortical and brainstem ischemic stroke.

Patients admitted with acute stroke will be recruited from the rehabilitation ward. Eligibility will be screened by the research team and the patients will be randomly allocated to the intervention group (real rTMS) or control group (sham rTMS) in a 1:1 ratio, with stratification into two subgroups according to the baseline Upper Extremities Fugl-Meyer Assessment (UE-FMA) score. The baseline evaluation (T0) will be performed by a blinded evaluator after group allocation. All participants will receive 30 min of intervention (real rTMS in the intervention group and sham rTMS in the control group), accompanied by 30 min of occupational therapy (OT) after the intervention. The intervention will be provided to participants for 10 consecutive working days. All participants will receive the same amount of occupational and physical therapy (PT) consisting of two sessions of 30-min OT and PT daily during this period. The evaluation will be performed at the end of the intervention period (T1) and 4 weeks after the end of the intervention (T2). The doses of OT and PT will be monitored and documented by the patient/caregiver at T1 and T2. An overview of the study design and process is shown in Figure 1.

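### Block size is fixed and published as 2 while the rTMS operator is unblinded, so informed site staff can deduce every second allocation; the block-size wording also conflicts

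*Protocol article*

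**What the plan says.** All of the following is in the protocol article.

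- **Strata (Randomization and blinding).** "Within each institution, the participants will be stratified into two subgroups based on a baseline UE-FMA score of 28". Two institutions and two UE-FMA groups give four separate lists.
- **Block size (same section).** Allocation is made "using a stratified block randomization method with blocks of size 2 within each stratum". The two arms are to be kept in a 1:1 ratio.
- **Block size again (same paragraph).** "The block size and seed number used will be randomly selected by a statistician responsible for the random assignment".
- **Concealment (same section).** "Random assignments will be stored in opaque envelopes for each participant and delivered to the coordinator at the start of the intervention".
- **Blinding (same section).** Participants and evaluators are blinded, and "the therapists who perform the treatment will also be blinded throughout the study". However, "the investigator who will perform rTMS will not be blinded to the assigned group".
- **Screening (Study design).** "Eligibility will be screened by the research team". The same section places the T0 evaluation, by a blinded evaluator, after allocation.
- **Sham (rTMS intervention; Discussion).** The sham uses the real coil turned perpendicular to the scalp, so whoever positions the coil necessarily knows the arm.

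**The concern.** Opaque envelopes protect an allocation only if it cannot be worked out by other means. With a known block size of 2 at 1:1, the second place in each pair is the complement of the first. The operator sees the arm of each patient he or she treats, so a sealed envelope adds nothing for the second member of a pair if the operator also knows the stratum and the order of entry.

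Two things are at stake. First, if a person with this knowledge could influence who is enrolled or when, predictable places could be filled selectively, and analysis cannot fully repair that. Secondly, masking becomes more fragile: one disclosed or correctly guessed arm exposes a second patient to anyone who can identify the pair-mate. Because T0 is measured after allocation, such a leak could touch both ends of the primary change score.

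Separately, a reader cannot tell from the paragraph whether the block size is fixed at 2 or drawn at random.

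**Working it through.** **Inputs.** Block size 2, ratio 1:1, two institutions by two UE-FMA groups (Randomization and blinding); 88 participants, 44 per institution (Participants and recruitment); difference 6.50, SD 10.30, 5% significance, 80% power, 10% dropout (Sample size).

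**The plan's own figure.** Taking the test as two-sided (sidedness is not stated), n per group = 2 × (1.960 + 0.842)² × 10.30² / 6.50² ≈ 39.4, so 40. Adding 10% gives 40 × 1.1 = 44 per group, 88 in total. The sample size reproduces, and the block size does not affect it.

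**Share of allocations fully determined by earlier ones.** For complete blocks of size 2m at 1:1, with the block size known, the expected share is 1/(m + 1).

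- Size 2 (m = 1): 1/2 = 50%, or 44 of 88.
- Size 4 (m = 2): 1/3 = 33.3%, or 29.3 of 88. Check: the fourth place is always determined, and the third is determined when the first two agree (probability 1/3), so (1 + 1/3)/4 = 1/3.
- Size 6 (m = 3): 1/4 = 25%, or 22 of 88.

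**Range for size 2.** A stratum with an odd count ends on an unpaired first place. If all four strata do so, (88 − 4)/2 = 42 are determined; if none does, 88/2 = 44. Hence 42 to 44.

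**Expected correct guesses.** The observer knows the earlier allocations in the stratum and guesses the arm with more places left, or tosses a coin when they are equal.

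- Size 2: (0.5 + 1)/2 = 75%, or 66 of 88.
- Size 4: (1/2 + 2/3 + 2/3 + 1)/4 = 70.8%, or 62.3 of 88.
- Size 6, by full enumeration: 68.3%, or 60.1 of 88.
- Sizes 4 and 6 mixed at random and unknown to the observer: about 68.5%, or about 60 of 88. This is a simulation that assumes 88/4 = 22 patients per stratum; the article does not give the split by UE-FMA group.
- Pure chance: 50%.

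**The two block-size statements side by side.** If the size is fixed at 2, random selection gives no protection. If one size was drawn once and happened to be 2, the sentences are compatible, but publication has still disclosed it. If sizes in fact vary, the statement of size 2 is wrong and the 50% falls. On each reading the text needs correcting or clarifying.

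**The case against.** The strongest reply is that predicting an allocation does harm only if the person who can predict it also decides who enters and when, and the article does not make that link. It says that the research team screens and that the rTMS investigator is unblinded. It does not say that these are the same people, that one operator treats every patient at a site, or that the operator enrols. A condensed article may leave such role separation to the full protocol. This stands: a reader might infer that selection bias is present, or that the operator screens patients, and the document supports neither.

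A reader might also infer that the envelopes conceal nothing, or that concealment fails outright for half the trial. That goes too far. The first allocation of every pair stays concealed, and the second is exposed only to someone who knows the earlier arm, the entry order and the stratum. Participants, therapists and evaluators are blinded, and nothing shows that they hold this information.

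It is tempting to attach a bias to the primary outcome. If the predictable places were filled with patients whose expected BBT change was shifted by 2 blocks up or down according to the coming arm, the arm difference would move by 2, which is 2/6.5 = 31% of the planned effect. The 2 has no source in the document. The sum assumes that every predictable place is steered, and it ignores the primary ANCOVA, which adjusts for T0 BBT and the UE-FMA stratum and would remove part of any selection on severity. The figure should not be used.

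Finally, larger blocks help only moderately. Informed guesses fall from 75% to about 68.5%, still well above 50%. This is why separation of roles belongs in the remedy. None of these replies removes the design fault or the wording conflict.

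**Conclusion.** The point holds in limited form. A block size of 2, fixed and disclosed, combined with an unblinded operator, lets informed site staff deduce 42 to 44 of 88 allocations with certainty, and ties the masking of each patient to that of a pair-mate. This rests on the size being 2 as stated, on 1:1 allocation within four strata, and on the observer knowing the earlier arm, the entry order and the stratum. It applies chiefly to the operator and possibly to the coordinator who receives the envelopes.

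Selection bias is a risk that the design leaves open. It is not shown, and the document gives no basis for sizing it. The statement that the block size is randomly selected must be reconciled with the fixed size whichever is true.

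**What to change.** For all remaining participants:

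1. The independent statistician generates a new list with randomly varying larger blocks, for example 4 and 6, within each institution by UE-FMA stratum. The sizes are not disclosed to the sites.
2. Delete the statement that blocks are of size 2, and say only that sizes vary and are held by the statistician.
3. State that the rTMS operator takes no part in screening, enrolment or outcome assessment.
4. Report how many patients were allocated under the old list.

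Fully determined allocations fall from 50% to at most about 25–33%; this is an upper bound because it presumes that the observer knows the block size. Informed correct guesses fall from 75% to about 68.5%.

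The cost is one new list from a statistician already engaged, a wording change and, if roles now overlap, some reassignment of site tasks. The statistical downside is a slightly larger possible imbalance within each stratum: up to 2 patients with blocks of 4 or 3 with blocks of 6, instead of 1. The sample size does not change.

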### Intervention

2.4.

#### rTMS intervention

2.4.1.

Patients will be seated comfortably in a chair during rTMS. The resting motor threshold (RMT) for the first dorsal interosseous muscle of the unaffected side will be measured over the contralesional M1 (c3 or c4 according to the 10–20 system). The RMT is defined as the minimum stimulation intensity required to evoke a response of at least 50 μV in at least 5 out of 10 consecutive stimulations (15). In each session, in the intervention group, the contralesional M1 will be stimulated through a 88-mm-diameter figure-of-eight coil powered by an ALTMS-A (Remed, Seongnam-si, Republic of Korea) with a frequency of 1 Hz and an intensity of 100% of the patient’s RMT measured in the contralesional M1 for 30 min, to achieve 1,800 stimuli per session. The stimulation intensity and duration were determined based on previous studies on low-frequency rTMS (16) and safety guidelines (8). For the control group, sham rTMS will be applied, and the coil will be positioned perpendicular to the scalp on the contralesional M1 with the same intensity and frequency as that in the real rTMS. The details of the rTMS system used in this trial are shown in Figure 2.

**Figure 2 fig2:**
[figure not shown]
Instruments and implementation of rTMS in this trial. **(A)** Depictive figure of actual rTMS implementation, 1: Transducer (a 88-mm-diameter figure-of-eight coil), 2: main body of ALTMS-A. **(B)** ALTMS-A system, 3: Transducer, 4: transducer holding arm, 5: LCD touch panel, 6: transducer output cable, 7: controller, 8: carrying wheel. **(C)** Left: Transducer front, Right: transducer rear, 9: magnetic field generator, 10: handle, 11: stimulation switch.

##### Implementation of occupational therapy

2.4.1.1.

OT will be provided twice a day for 30 min each, starting within 10 min after rTMS in both the intervention and control groups between T0 and T1. Participants will receive one-on-one OT with an occupational therapist, comprising task-oriented therapy, including shaping exercises. The difficulty will be tailored to each participant and will be gradually increased according to the improvement in the motor function of the paralyzed hand. Therapists will be blinded to the participant groups throughout the trial. Participants will be provided with a rehabilitation diary, and the therapy dosage will be recorded during the period between T1 and T2. In the rehabilitation diary, the date and duration of rehabilitation treatment in minutes will be recorded as items of occupational therapy, physical therapy, or other treatment.

### Outcomes

2.5.

#### Primary outcome measure

2.5.1.

Primary outcome is the amount of change in the number of Box and Block Test (BBT) (17) at T2 compared to that at T0 (3, 5, 13, 18). The BBT is a manual dexterity test that has been used to evaluate physically disabled individuals. The BBT consists of a partition and wooden box divided into two compartments containing 150 blocks. Participants will be asked to move as much as possible, one at a time, from one compartment of the box to another of the same size, within 60 s. The BBT score is the number of blocks the participant has moved (17).

#### Secondary outcome measures

2.5.2.

Several secondary outcome measures will be assessed (Table 2), including: changes in the number of BBT at T1 compared to those at T0; UE-FMA (19) score changes at T1 and T2 compared to those at T0 (3, 13, 20); changes in the Korean version of Modified Bartherl Index (K-MBI) (21) score at T1and T2 compared to those at T0 (13, 22); changes in the NIH Stroke Scale (NIHSS) scores (23) at T1 and T2 compared to those at T0 (12, 13, 24); the finger tapping test (FTT) (25) (participants tap their index fingers as quickly as possible within a 10-s time interval, and the number of times they tap their fingers becomes an FFT score) score changes at T1and T2 compared to those at T0 (13, 24); the Brunnstrom Stage (26) changes at T1and T2 compared to those at T0 (13); the Modified Ashworth Scale (MAS) score changes at T1and T2 compared to those at T0 (13, 22, 27); and the degree of change in grip strength (hand grip, pinch grip, lateral pr, and three-jaw chuck) measured using the JAMAR dynamometer (Performance Health Supply Inc., Cedarburg, United States) at T1 and T2 compared to that at T0 (3, 13, 22).

**Table 2 tab2:** Timetable and measures to be made.

	Intervention period		4 weeks after EOT (T2)
	Baseline (T0)	EOT (T1)	
**Primary outcome measure**			
Box Block Test	√	√	√
**Secondary outcome measures**			
Upper extremity FMA	√	√	√
K-MBI	√	√	√
NIHSS	√	√	√
Finger Tapping Test	√	√	√
Brunnstrom stage	√	√	√
Modified Ashworth scale	√	√	√
Grip strength	√	√	√

EOT, end-of-treatment; FMA, Fugl-Meyer Assessment; K-MBI, Korean version of the Modified Barthel Index; NIHSS, National Institutes of Health Stroke Scale.

### Sample size

2.6.

According to a previous study (13), the average change in BBT at 1 month after baseline was confirmed to be 17.40 (9.80) in subcortical and brainstem stroke subjects who underwent rTMS and 10.90 (10.30) in subjects who received sham stimulation. The average change in BBT in the intervention and control groups in this clinical trial is also expected to be similar, and the standard deviation is assumed to be a large value of 10.30 for the conservatively setting. Assuming a significance level of 5% and a power of 80% under a BBT average change of 6.50 (intervention group: 17.40, control group: 10.90) and a standard deviation of 10.30, the number of subjects calculated is at least 40 per group; therefore, a total of 88 subjects will be recruited, considering a 10% dropout rate.

### Data management and sharing

2.7.

All participants’ data will be collected by research team members and will be stored as form of an Electronic Case Report Form (eCRF) in secured network cubeCDMS^®^ system (CRScube Inc., Seoul, Korea). The backup database will be updated regularly, and only the research team will have access to it. Case report forms will be stored in the research team’s locked cabinet. After completing the eCRF entry, the data will be frozen, and locked if there are no abnormalities. The collected data will be recorded on a CD and sent to Seoul National University Bundang Hospital and Chungnam National University Hospital.

### Primary hypothesis and data analysis

2.8.

#### Primary hypothesis

2.8.1.

The primary hypothesis of the study is that the change in the number of BBT, at T2 compared to that at T0 in the intervention group that received real rTMS and occupational therapy, would be significantly greater than that in the control group that received sham rTMS and occupational therapy.

#### Analysis of demographic and other underlying data

2.8.2.

Demographic and other characteristics will be analyzed using a group targeting the full analysis (FA) set. Analysis will be performed on survey items at the time of screening, including demographic survey, social history survey, vital signs, physical examination, medical history, surgical history evaluation, Brunnstrom stage (26), and K-MMSE (28) evaluation. In addition, for continuous variables, the number of participants, average, standard deviation, median, minimum, and maximum values, and for categorical data, frequency and fraction will be presented in both total and groups. Statistical significance of differences between groups will be analyzed using an independent two-sample *t*-test for continuous data (Wilcoxon rank sum test if the normality distribution assumption is not satisfied) and chi-square test for categorical data.

#### Analysis of primary outcome

2.8.3.

Descriptive statistics (number of participants, mean, standard deviation, median, minimum, and maximum) of the BBT values at T0 and T2 and the degree of BBT change between T0 and T2 will be presented by group. The statistical significance of BBT changes between groups will be confirmed by analysis of covariance (ANCOVA) with the number of BBTs at T0 and stratified variables (depending on whether the UE-FMA score is less than 28 points) and occupational therapy dosage between T1 and T2 as covariates. Additionally, in the subgroup analysis, the location of stroke lesions will also be included as a covariate in the ANCOVA. All statistical analysis will be performed with significance level of 0.05.

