### Participants and recruitment

2.2.

In this study, the authors will enroll 88 adult participants, from two institutions recruiting 44 participants each: Seoul National University Bundang Hospital (Gyeonggi-do, Republic of Korea) and Chungnam National University Hospital (Daejeon, Republic of Korea).

The inclusion criteria are as follows: (a) between the ages of 19 and under 80, (b) within 90 days from first subcortical or brainstem ischemic stroke confirmed by Computed Tomography (CT) or Magnetic Resonance Image (MRI) (13), (c) UE-FMA score exceeding 15 points (14), and (d) Korean version of Mini Mental Status Exam (K-MMSE) score of 15 or higher. The exclusion criteria are as follows: (a) diagnosis of a cerebellar stroke, (b) history of cerebrovascular surgery, (c) wrist score of less than 1 and hand score of less than 1 (13), (d) history of psychiatric or neurological disease before stroke onset, (e) inability to undergo rehabilitation treatment for other reasons, such as medical problems, and (f) history of epilepsy or seizure disorder. The detailed inclusion and exclusion criteria are listed in Table 1.

**Table 1 tab1:** Major inclusion and exclusion criteria.

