We also stratified the participants into two subgroups based on the initial UE-FMA score because it has been reported that rTMS can be less effective in patients with stroke with severe upper extremity paralysis. Ludemann-Podubeck et al. (35) insisted that when a larger part of the M1 or its corticospinal projections is involved in stroke, causing a more profound clinical hand motor deficit, the contralesional dorsal premotor cortex may have a positive influence on motor recovery. Therefore, low-frequency rTMS of the contralesional M1 may not help to restore functionality (35). Two other studies referred to the same mechanism and explained the correlation between the degree of paralysis and the effect of rTMS (36, 37). Based on these results, we excluded patients with stroke with extremely severe upper extremities paralysis (UE-FMA score of 15 or less and those with a wrist score of less than 1 and a hand score of less than 1) and stratified into two subgroups (UE-FMA score of 28 or higher and UE-FMA score below 28) to ensure that the initial severity in both the intervention group and control group is evenly distributed.

In this clinical trial, the change in the number of BBT at 4 weeks after EOT compared with that at baseline has been set as the primary efficacy evaluation variable. The BBT has been used in various rehabilitation studies since 1994, when its reliability and validity were verified as measures of hand function in the elderly (38); it is often used as a clinical variable to confirm hand function status and total agility of the upper limb, especially in patients with stroke (3). Accordingly, BBT has also been used as an effectiveness evaluation variable in various studies to evaluate the recovery of upper limb motor function using rTMS in patients with stroke (3, 5, 13, 18). The UE-FMA is more useful in assessing abnormalities of movement, whereas the BBT is more suitable for evaluating activity limitations (39). However, with UE-FMA, it is difficult to confirm the response to the treatment of patients with stroke with mild upper limb hemiplegia due to the ceiling effect. Therefore, in this study, the primary outcome measurement has been chosen as the change in the BBT.

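### Randomisation is stratified by institution, but the primary and secondary ANCOVAs leave institution out; if institution is prognostic, the test is mildly conservative and some power is forgone.

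*Protocol article*

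**What the plan says.** Section 2.3 (Randomization and blinding) sets up two stratification factors: "Within each institution, the participants will be stratified into two subgroups based on a baseline UE-FMA score of 28". Allocation is 1:1, "with blocks of size 2 within each stratum". Section 2.2 takes patients "from two institutions recruiting 44 participants each". The Discussion gives the severity strata as "UE-FMA score of 28 or higher and UE-FMA score below 28".

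Section 2.8.3 (Analysis of primary outcome) lists the ANCOVA covariates by name. They are baseline BBT, "stratified variables (depending on whether the UE-FMA score is less than 28 points", closing the bracket there, and "occupational therapy dosage between T1 and T2 as covariates". Section 2.8.4 (Analysis of secondary outcome) defines the stratification variables in the same way. Institution is in neither list. The Abstract and section 2.1 also mention only UE-FMA when they describe the stratification.

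**The concern.** The plan puts the randomisation strata into the model but defines them as one factor, when the design has two. Separate lists in small blocks make the arms almost equal in number within each hospital, so a difference between hospitals hardly enters the treatment contrast. An ANCOVA without institution nevertheless leaves that difference in the residual variance. The reported standard error then ignores precision that the design has already secured.

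What is at stake is efficiency in the confirmatory test. Two hospitals may differ in case mix, ward routine or assessors, and any part of this that the listed covariates do not absorb would widen the confidence interval for no benefit.

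**Working it through.** **Inputs from the protocol.** Section 2.6: difference 6.50 blocks, SD 10.30, significance level 5%, power 80%, 40 per group, 10% dropout, 88 in total. Section 2.2: two institutions of 44. Section 2.3: 1:1 allocation, blocks of 2. Sidedness is not stated; a two-sided test reproduces the planned number, while a one-sided test would give 32 per group.

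**The plan's own figure.** n = 2(1.960 + 0.842)² × 10.30² / 6.50² = 39.4, so 40 per group. Then 40 × 1.1 = 44 per group, or 88. The stated numbers reproduce.

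**Assumption.** R² is the share of the variance of BBT change that is due to institution. The documents do not give it. With two equal institutions and total SD 10.3, R² corresponds to a mean difference between them of 2 × 10.3 × √R²: 2.1 blocks at 1%, 4.6 at 5%, 6.5 at 10% and 9.2 at 20%.

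**Formulas (normal approximation, arms balanced within institution).**
- SE reported without institution: 10.3 × √(2/40) = 2.303.
- True SE: 2.303 × √(1 − R²), so reported/true = 1/√(1 − R²).
- True type I error without institution: 2[1 − Φ(1.96/√(1 − R²))].
- Power without institution: Φ[(6.5/2.303 − 1.96)/√(1 − R²)].
- Power with institution: Φ[6.5/(2.303√(1 − R²)) − 1.96].

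Example at R² = 10%, where √0.9 = 0.9487. The SE ratio is 1/0.9487 = 1.054. Power without institution is Φ(0.862/0.9487) = 81.8%, and with institution Φ(2.822/0.9487 − 1.96) = 84.5%.

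| R² | SE too large by | True type I error | Power without institution | Power with institution | Forgone (points) |
|---|---|---|---|---|---|
| 0 | 0 | 5.0% | 80.6% | 80.6% | 0 |
| 1% | 0.5% | 4.9% | 80.7% | 81.0% | 0.3 |
| 5% | 2.6% | 4.4% | 81.2% | 82.5% | 1.3 |
| 10% | 5.4% | 3.9% | 81.8% | 84.5% | 2.7 |
| 20% | 11.8% | 2.8% | 83.3% | 88.4% | 5.1 |

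**Simulation with the ANCOVA itself.** This used 80 completers, two institutions and blocks of 2 in each stratum, with baseline BBT and the UE-FMA stratum in the model. The UE-FMA cut was placed at the median (assumption), UE-FMA was unrelated to the outcome, and occupational therapy dosage was left out.
- R² = 0: type I error is 5.3% without institution and 5.2% with it.
- R² = 10%: without institution, mean model SE 2.31 against empirical SE 2.22, type I error 3.9%, power 79.8%. With institution, model SE 2.19 against empirical 2.22, type I error 5.1%, power 82.2%.

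At R² = 10% the empirical SE is the same either way (2.223 and 2.222). The blocks already deliver the balance; only the reported SE fails to credit it.

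**The case against.** **The effect may be small or nil.** This stands. The problem exists only if institution is prognostic after adjustment, and no figure supports that. Baseline BBT and the UE-FMA stratum absorb part of any case-mix difference. Therapy is set equal during treatment, and later occupational therapy dosage is a covariate. The residual institution effect may therefore lie at the low end of the table.

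**A SAP may deal with it.** This does not remove the point. The article does not leave the covariates open; it names them, says that the stratification variables are included, and then defines those as one of the two factors.

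**A reader might infer that planned power falls well below 80%.** Adding a site difference of 5, 8 or 10 blocks on top of SD 10.3 gives power without institution of about 78%, 75% and 73%. But this inflates the total SD to √(10.3² + D²/4), that is 10.6, 11.05 and 11.45. Section 2.6 gives 10.30 as the SD of the change score and does not say that site variance was removed. With the total SD held at 10.3, simulated power without institution is 80.4%, 81.2% and 82.7%, against 82.1%, 85.7% and 89.0% with it. A gain is forgone; the planned power is not eroded. Differences of 8 and 10 blocks also exceed the assumed treatment effect of 6.5.

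**A reader might infer that the two-level UE-FMA also mis-states the standard error.** It does not, because it is exactly the factor used at randomisation. In the simulations, continuous UE-FMA added to a model with institution lowers the model SE by 0.6–1.0% at an assumed correlation of 0.3 with BBT change, and raises it by about 0.7% at zero correlation.

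**Conclusion.** The mismatch is real and can be read directly from sections 2.3, 2.8.3 and 2.8.4: institution is a stratification factor and is missing from a covariate list that is otherwise explicit. The consequence is modest and runs in the conservative direction. For R² of 1% to 10%, the standard error is 0.5% to 5.4% too large and 0.3 to 2.7 power points are forgone. These figures rest on an assumed R², a total SD of 10.3, 40 evaluable patients per group and near-perfect balance within institution.

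The documents do not support a claim of bias or of inflated false positives. Nor is it an error to omit continuous UE-FMA or days since stroke. Neither was a randomisation factor in that form, and any gain from them rests on assumed correlations. They are optional refinements outside this point.

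**What to change.** Before unblinding:
- Add institution as a fixed effect to the primary ANCOVA and to every secondary ANCOVA.
- Correct the definition of the stratification variables in sections 2.8.3 and 2.8.4 so that it names both institution and the UE-FMA stratum (below 28; 28 or higher).
- Keep the two-level UE-FMA stratum as it is.

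The cost is a wording change and one degree of freedom. With 80 completers, the primary model as written has 80 − 5 = 75 residual degrees of freedom (intercept, treatment, baseline BBT, UE-FMA stratum, therapy dosage), and 74 after the change. No new data are needed and the sample size stays at 88.
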